**METHODS**

**Design**

This will be a double-blind sham-controlled two-arm randomized clinical trial. Fifty participants will be randomized (1:1) to each arm. Arm 1 will be active tDCS plus varenicline (n=25) and Arm 2 will be sham tDCS plus varenicline (n=25). Treatment duration will be 12 weeks. Subjects will be required to attend an in person assessment visit. They will then be randomized to a condition. Neuroimaging scans (fMRI) and eye-tracking tests will be conducted in all participants at baseline. Participants will undergo two scans at baseline on different days within the same week: one in a satiated state and one in a non-satiated state. The same tasks will be performed at each scan. s. Following the baseline fMRI scans and eye-tracking tests, subjects will start taking the varenicline simultaneous with starting the tDCS regimen whereby they will come to the clinic every day (Monday to Friday) for the first 2 weeks to undergo the stimulation (active: 20 minutes at 2mA, sham: 30 seconds at 2mA and then nothing). Their target quit date will be at the end of this 2 week period. They will return to the clinic every two weeks for the next 10 weeks for a booster tDCS session and to complete questionnaires. Eye tracking tests will be conducted at the end of the fourth and eighth weeks. At the end of the 12-week treatment period they will undergo a third fMRI scan and eye-tracking tests. For the next 14 weeks they will be contacted weekly by e-mail or text message to report on their smoking status as measured by the 7 day point prevalence abstinence question. “Have you had a cigarette, even a puff, in the last 7 days?” At the 6-month time point subjects will be asked to return to the clinic for a brief visit to confirm smoking abstinence using expired CO and urinary cotinine and to complete questionnaires.

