**Sample Size and Power Calculation**

If we assume a 40% abstinence rate at end of treatment in the varencline plus sham tDCS group, the abstinence rate in the active tDCS group would need to be double that or 80% in order to see a statistically significant difference with n=25 per arm, p <0.05, and 80% power. As such we do not expect to see a statistically significant difference between the two treatment arms at 25 subjects per arm.

For the treatment part of the study, the main purpose of the study is to establish an Effect Size for tDCS as an adjunct to standard varenicline treatment. This is independent of the number of subjects but allows us to estimate the N that would be required to achieve statistical significance depending on the effect size we observe. The effect size measure we will use will be the partial η2 generated by SPSS and is described in greater detail below.

For the MRI portion of the study, 15 to 25 subjects per group is standard in the neuroimaging field and is more than sufficient to detect significant within- and between-group differences in brain activity.

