**Data Analysis**

Continuous data (cravings, mood, cigarettes smoked/day, CO) will be assessed with 2 Gender x 2 (Laterality) x 10 (session) Analyses of Variance (ANOVA). Parallel ANOVAs will assess self-report measures during post-treatment follow-up. Categorical data (e.g., # abstinent participants/session) will be assessed with chi-square, and Kaplan-Meyer survival analysis for repeated measures. Planned comparisons will be performed for the critical experimental conditions (active tDCS) vs. sham.

The critical metric will be Effect Size (partial η2 generated by SPSS), rather than p level. This will reveal the degree of efficacy for the primary outcome variable, Consecutive Days Abstinent (small = .01, medium = .06, large = .14), and allow us to estimate N required to achieve statistical significance for this effect (80% power, α = .05, two-tailed). Pearson correlations will explore the possible relationship between effects of tDCS (session 10 scores, controlling for session 1) and trait factors (e.g., FTND, age, gender, depression).Analysis of MRI data

For the neuroimaging data, brain imaging measures will be compared between groups and across time points, using analysis of variance. MRI measures will also be related to subjective responses (i.e., baseline scores and changes in craving, mood, and withdrawal) using linear regression.

fMRI data will be analyzed by fitting a general linear model (GLM) to the data time-series at every voxel across the brain (and/or within ROIs) and assessing effects using F/t-tests and % signal change calculations. Quantitative T1 maps and DTI analysis will be analyzed at the whole brain level and using ROIs.

After back-sorting by treatment outcome (achieved/maintained abstinence), we expect baseline measures to predict relapse, and active tDCS treatment to result in more efficient functional activation, . than sham tDCS at the second MRI scan.

Analysis of Eye-Tracking Data

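### The efficacy reading rests on a size label for partial eta-squared, which carries no direction and whose lowest band, with 25 per arm, cannot be told from chance

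*Protocol*

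**What the plan says.** The Protocol, Sample Size and Power Calculation, states that a significant difference is not expected with 25 per arm. For the treatment part, "the main purpose of the study is to establish an Effect Size for tDCS as an adjunct to standard varenicline treatment". Of that effect size it adds: "This is independent of the number of subjects but allows us to estimate the N" needed for significance.

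The Data Analysis section names the measure: "The critical metric will be Effect Size (partial η2 generated by SPSS), rather than p level". It then states how the measure is to be read: "This will reveal the degree of efficacy for the primary outcome variable, Consecutive Days Abstinent (small = .01, medium = .06, large = .14". It also gives the measure a planning use, to "allow us to estimate N required to achieve statistical significance for this effect (80% power, α = .05, two-tailed").

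Neither section attaches a sign, a confidence interval or a condition that active be ahead of sham. The Hypotheses and Outcome Measures sections are directional: active tDCS is expected to give more abstinence. Data Analysis also lists planned comparisons of active with sham, chi-square tests and survival curves, but does not link any of them to the effect-size reading.

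**The concern.** The figure chosen to express efficacy cannot distinguish the trial's hypothesis from its reverse. If sham does better by some amount, partial eta-squared, its label and the N derived from it are the same as if active had done better by that amount.

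The second weakness is separate and comes from sampling error, not from the missing sign. The lowest band is so low for 50 participants that an inert treatment reaches it about as often as not. A *small* degree of efficacy would then be reported on evidence that does not separate a small effect from none, in a trial whose stated main purpose is to establish this effect size and plan from it.

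**Working it through.** **Inputs.** Design: "Fifty participants will be randomized (1:1) to each arm", which the next sentence makes 25 per arm. Cut-offs .01, .06 and .14 from Data Analysis. Control rate from the sample size section: "If we assume a 40% abstinence rate at end of treatment in the varencline plus sham tDCS group". Planning at 80% power and two-sided .05.

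**The plan's own figure.** For 40% versus 80% with 25 per arm, power is 0.845 by the normal approximation, 0.867 by the exact uncorrected chi-square and 0.788 by Fisher's exact test. The stated 80% is reproduced, and it is not in dispute.

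**Direction.** For a yes/no outcome in two equal arms, eta-squared equals phi-squared = (difference)² / [4 × p̄(1 − p̄)], where p̄ is the pooled proportion. Take 13 of 25 abstinent on one arm and 10 of 25 on the other: difference 0.12, p̄ = 0.46.
- phi-squared = 0.0144 / (4 × 0.2484) = 0.0145, labelled *small*.
- Implied d² = 4 × 0.0145 / (1 − 0.0145) = 0.0588.
- N per arm = 2 × (1.960 + 0.842)² / 0.0588 = about 267.

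Every line is identical whether the 13 are on active or on sham. At the cut-offs themselves, the same formula gives about 389, 62 and 25 per arm, again whichever arm is ahead.

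**Chance.** With no true effect and two groups, eta-squared = F / (F + df) with F ~ F(1, df), so P(eta-squared ≥ c) = P(F ≥ df × c / (1 − c)). With df = 48 the F thresholds are 0.485, 3.064 and 7.814.

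| No true effect | ≥ .01 | ≥ .06 | ≥ .14 |
|---|---|---|---|
| df 48 (two arms, 50 analysed) | 49.0% | 8.6% | 0.7% |
| df 46 (gender and its interaction added) | 49.9% | 9.3% | 0.9% |
| df 38 (assumed: 40 analysed) | 53.9% | 12.8% | 1.7% |
| Yes/no outcome, 40% in both arms, exact | 47.1% | 9.1% | 0.7% |
| Skewed days abstinent, simulated (assumed shape) | 48.5% | 8.6% | 0.8% |

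By symmetry half of each figure has sham ahead. At df 48 that is 24.5% for at least *small*; in the exact yes/no calculation it is 23.6%. The protocol does not fix the error df for this outcome, hence the range.

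**Dependence on N.** The mean of the sample eta-squared under no effect is 1 / (df + 1) = 1/49 = 0.020, twice the *small* cut-off, and it rises as N falls. The statement that the measure is independent of the number of subjects does not hold for the sample statistic.

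**The case against.** This is a pilot. It seeks preliminary evidence, expects no significant result, and defines no threshold for declaring efficacy and no go/no-go step. The cut-offs are benchmarks in brackets. The planned active-versus-sham comparisons, the abstinence counts and the survival curves would show any reader which arm did better, and the hypotheses fix the expected direction. A statistical analysis plan, not at hand, may add signs and intervals.

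Most of this stands. A reader might infer that the protocol would declare tDCS effective in half of all trials of an inert treatment, or would report a sham advantage as tDCS efficacy. The documents do not support that: there is no decision rule, and the authors would have to disregard their own counts and curves. Nor does the figure of about one half describe all the labels. It applies to *small* or above only. If active must also be ahead, the chances under no effect fall to 24.5%, 4.3% and 0.4%.

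What remains is that the protocol itself fixes the metric, its cut-offs and its interpretation as a degree of efficacy, and leaves direction and precision outside that interpretation. This is a choice already made in the text, not a detail deferred to a later plan.

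**Conclusion.** The point holds as a badly fixed metric, worth changing before analysis. The lack of sign follows from the definition of partial eta-squared and needs no assumption. The chance rates assume no true effect, 25 per arm and a simple comparison of arms. They change little with the error df or the form of the outcome: 47% to 54% for at least *small*, about 9% to 13% for at least *medium*, and about 1% to 2% for *large*, where the upper ends rest on the assumed 40 analysed. *Large* is hard to reach by chance; *small* is not informative. The claim goes no further than this: the stated efficacy reading, taken alone, separates neither benefit from harm nor a small effect from none.

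**What to change.** - Make the critical metric the signed active-minus-sham difference in the primary outcome, with its 95% confidence interval. As Outcome Measures defines that outcome, this is the difference in the proportions continuously abstinent in weeks 9–12. State openly that it replaces Consecutive Days Abstinent, which Data Analysis names as primary, so that the conflict between the two sections is settled by decision.
- Drop the small/medium/large labels as a reading of efficacy. Report partial eta-squared, if wanted, only as a supplement with the direction stated.
- Size the next trial from the signed difference and its interval.
- Do not make any description of efficacy depend on the whole interval excluding zero. That would be a significance test, which the sample size section already expects to fail.

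The cost is wording only: no new data, visits or participants. The downside is a result that looks less conclusive. At 40% in both arms the half-width is 1.96 × √(2 × 0.4 × 0.6 / 25) = 0.27, about 27 percentage points. In the example of 13 versus 10 quitters, the report would read +12 points (about −15 to +39) with active ahead, and −12 points (about −39 to +15) with sham ahead, where the present plan gives one label for both.

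### The trait correlations treat the adjusted session-10 score as the effect of tDCS, so they show correlates of response in general and not who benefits over sham

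*Protocol*

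**What the plan says.** Under Data Analysis the protocol says that Pearson correlations will explore a possible relationship between "effects of tDCS (session 10 scores, controlling for session 1) and trait factors". The traits are given as examples: "trait factors (e.g., FTND, age, gender, depression". The parenthesis after the word effects is the only definition of the tDCS effect for this analysis. It does not say whether the two arms are pooled, analysed separately, or restricted to active tDCS.

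Two other analyses in the same section come near the question:
- The continuous outcomes go into "2 Gender x 2 (Laterality) x 10 (session) Analyses of Variance (ANOVA".
- The arm contrast is stated as "Planned comparisons will be performed for the critical experimental conditions (active tDCS) vs. sham", with no trait involved.

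Under Design, "subjects will start taking the varenicline simultaneous with starting the tDCS regimen", and this applies to both arms. The Pharmacological treatment section places the varenicline dose escalation in the same two weeks as the ten daily sessions and sets the target quit date on the last day of that period. Allocation is 1:1 with 25 per arm.

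**The concern.** A treatment effect is a contrast between what happens under active tDCS and what happens under sham. One participant's session-10 score, even after adjustment for session 1, contains no such contrast. Between session 1 and session 10 every participant also starts varenicline, prepares to quit and passes through two weeks of daily clinic contact. A trait linked to craving, mood or smoking under any treatment will correlate with that score whether or not it has anything to do with tDCS.

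Adjusting for session 1 removes differences in starting level. It does not supply the missing sham comparison.

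The trial is a pilot meant to inform a larger one. If a merely prognostic trait is written up as related to the effects of tDCS, that label could steer eligibility, stratification or subgroup plans in the next trial.

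**Working it through.** **The plan's own figure.** The trait analysis has no power or precision figure. The only one in the protocol is for abstinence, 40% against 80% with 25 per arm, and this point does not depend on it. It reproduces adequately: n = [1.96·√(2·0.6·0.4) + 0.84·√(0.4·0.6 + 0.8·0.2)]² / 0.4² ≈ 22.3, so 23 per arm. Exact power with Fisher's test at 25 per arm is 78.8%.

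**Inputs from the protocol.** 25 per arm; session-10 score adjusted for session 1; Pearson correlation with a trait; varenicline in both arms.

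**Assumed, because the protocol gives no figures.** Trait and session-1 score standard normal; session-1 slope 0.5; residual SD 1; arm effect 0.5 SD; trait slopes as listed below; two-sided 0.05; 4,000 simulated trials per scenario. At that number of trials the Monte Carlo standard error is at most √(0.5·0.5/4000) = 0.8 percentage points, so differences of a point or two between runs are noise.

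**Step 1: what the correlation estimates.** Let the score be 0.5·S1 + b·T − 0.5·A + error, with the same trait slope b in both arms and therefore no moderation. The arm term contributes variance 0.5²·0.25 = 0.0625 to the pooled residual. The pooled partial correlation with T is b / √(b² + 1 + 0.0625):
- b = 0.3: 0.3 / √1.1525 = 0.28
- b = 0.5: 0.5 / √1.3125 = 0.44

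The simulated means were 0.279 and 0.436. The quantity is clearly non-zero although the true modification of the tDCS effect is exactly zero.

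**Step 2: how often each analysis gives p < 0.05.** The comparison model is session-10 score on session-1 score, arm, trait and arm × trait.

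| Trait slope (sham / active) | Correlation, pooled | Correlation, active arm only | Arm × trait |
|---|---|---|---|
| 0.3 / 0.3, no moderation | about 51% | about 29% | about 5% |
| 0.5 / 0.5, no moderation | about 90% | about 61% | about 5% |
| −0.4 / +0.4, full reversal | about 7% | about 45% | about 74% |
| 0 / 0.3, active arm only | about 16% | about 29% | about 16% |
| 0 / 0.5, active arm only | about 37% | about 61% | about 38% |
| 0 / 0.8, active arm only | about 67% | about 93% | about 75% |

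**Step 3: reading the table.** An active-arm correlation depends only on the slope in the active arm. It is therefore the same for a trait with slopes 0.3 / 0.3 (pure prognosis) as for one with slopes 0 / 0.3 (pure moderation), and likewise at 0.5. It cannot tell the two apart. The pooled correlation estimates the average slope. That average is large for a purely prognostic trait and is (−0.4 + 0.4)/2 = 0 for a full reversal.

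**Step 4: precision of the alternative.** The standard error of the slope difference is roughly √(1/25 + 1/25) = 0.28 residual SD. The 95% CI half-width is then about 2.01·0.28 = 0.57, slightly more once estimation of the other terms is counted. This matches the low interaction power of about 16% to 38% for active-only slopes of 0.3 to 0.5.

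**The case against.** The strongest reply is that the protocol only says it will explore a possible relationship. No research question or hypothesis asks whether FTND, age, gender or depression modifies the tDCS effect, no rule for declaring a moderator is set, and effect size is named as the critical metric rather than the p level. That stands as a limit on importance, and a reader should not infer that the plan commits to declaring moderators. It does not rescue the definition: on an effect-size reading, a purely prognostic trait still gives a correlation of 0.28 to 0.44 under a label that attributes it to tDCS.

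Second, a reader might infer that the arms are pooled. The protocol does not say so, and an active-arm reading is possible. The pooled percentages then do not apply, and the cancelling of opposite slopes does not arise. The confusion of prognosis with benefit over sham remains, at 29% to 61%.

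Third, a reader might infer that true moderators would generally be missed. The 7% against 74% result needs a pooled analysis and a full reversal between arms, which nothing in the protocol suggests. For a trait that matters only under active tDCS, the pooled correlation is significant about as often as the interaction (16% to 67% against 16% to 75%). What it lacks is the ability to label the result as moderation.

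Fourth, the ANOVA may already cover gender. Both arms use the same electrode placement, so Laterality may be a leftover label for arm, and gender × arm would then be in the model. That is uncertain and does not reach FTND, age or depression.

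Finally, a SAP that is not shown could add interaction terms or state which arms are used. The definition of the effect, however, is fixed in the protocol itself.

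**Conclusion.** The point holds as a secondary, exploratory weakness. The stated analysis answers a different question from the one its wording claims: it finds correlates of response to the whole treatment package and cannot show who benefits from tDCS over sham. This conclusion follows from the definition and does not depend on pooling or on any assumed number.

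The size of the false-attribution risk does depend on assumptions. With equal slopes of 0.3 to 0.5 SD in both arms and 25 per arm, it is about 51% to 90% pooled and 29% to 61% in the active arm alone, against about 5% for the interaction. Smaller prognostic slopes would give smaller figures. The simulation used a continuous trait, so the percentages are only indicative for gender.

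The documents do not support the stronger reading that the plan would be wrong in both directions as a rule, or that its main results are at risk. The primary abstinence comparison, the sample size and the main effect estimate are untouched.

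**What to change.** Replace the sentence on Pearson correlations with an exploratory linear model, fitted for each trait: session-10 score on session-1 score, arm, trait and arm × trait, using both arms. Report the interaction estimate with its 95% CI as the exploratory measure of moderation. Report the trait's overall association separately, labelled as a predictor of response in general. State in the same paragraph whether Laterality in the ANOVA means treatment arm.

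The cost is a change of wording in the analysis section, with no new data or visits. The drawback is imprecision: at n=50 the interaction has power of only about 16% to 38% for active-only slopes of 0.3 to 0.5, so it should be read as an estimate to inform a later trial and not as a test.

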**Hypotheses**:

1. The combination of varenicline treatment plus tDCS to the left DLPFC will improve smoking cessation outcomes and relapse rates in treatment seeking smokers.
2. Active tDCS will reduce fMRI BOLD response to smoking cues compared to baseline within-subjects and compared to sham tDCS between subjects. Those who quit smoking in the last 4 weeks of treatment will show a “normalization” of brain reactivity to smoking cues and reward anticipation relative to those who were unable to remain abstinent over the short term due to tDCS extinguishing the salient properties of smoking-related cues and reward anticipation.
3. Compared to baseline, varenicline treatment will reduce within subject attentional bias, as measured by parameters of visual scanning behavior (VSB), to smoking and negative emotional cues.
4. Active tDCS will reduce attentional bias to smoking and negative emotional cues compared to sham tDCS. Those who quit smoking in the last 4 weeks of treatment will show “normalized” attentional bias patterns to smoking cues and reward anticipation relative to those who were unable to remain abstinent over the short term. Subjective measures of cravings will be correlated with within-subject changes in attentional bias to smoking cues and reward anticipation.
5. Individuals with larger changes in attentional bias to smoking-related cues and/or negative emotional cues, and lower measures of attentional bias to high-arousal/high-risk cues will have higher rates of abstinence (less relapse). Attentional bias will be measured by parameters of visual scanning behaviour and through the analysis of visual scanning patterns (sequences of fixations).
6. The probability of remaining abstinent over the long term will be inversely correlated with VSB measures of novelty seeking behavior.
7. Active tDCS will reduce impulsivity compared to sham tDCS as measured by higher delayed discounting scores.

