**Participants**

Study participants will be 50 treatment seeking daily dependent smokers willing to make a quit attempt in the next 30 days. They will be recruited from our Nicotine Dependence Clinic and from the Greater Toronto Area through paid advertising in local newspapers and through the CAMH Registry and the CAMH website. Participants will have no concurrent Axis I psychiatric disorder (or history of substance use disorder), based on SCID, and be free of psychoactive drugs and medications, based on self-report and urinalysis. To ensure against subtle neurological deficits associated with sub-clinical alcohol misuse, men will be required to drink no more than 12 standard drinks per week and women will be required to drink no more than 9 drinks per week. These values conform to safe drinking limits for non-problem drinking (Sobell and Sobell, 1992). According to standard protocols for tDCS clinical trials, participants will also be excluded if they: a) have had recent clinically significant head trauma; b) have a history of seizures and/or epilepsy; c) are pregnant or planning to become pregnant; d) have pacemakers or implanted electrical devices such as cochlear implants; e) have metal embedded in the skull; or f) have skin lesions, open wounds, bruising, or similar injuries at either of the stimulation sites.

*Eligibility Criteria*

- Male or female
- Ages 19-65
- Daily smoker > 8 CPD
- Seeking treatment to quit smoking
- No current/recent DSM-IV Axis I diagnosis (apart from nicotine dependence)
- No current use of psychoactive drugs or medications
- No current use of Nicotine Replacement Therapy, e-cigarettes, or other medications for smoking cessation
- No history of seizures/epilepsy
- No metal embedded in the skull and/or implanted electrical devices
- No head injury (no concussion – diagnosed by a physician; OR no blow to the head with loss of consciousness for more than 1 hour)
- No known contraindications to fMRI
- No known contraindications to Varenicline
- Able to attend daily appointments for tDCS for the first 2 weeks and then once every 2 weeks for the next 10 weeks.
- Willing to undergo three fMRI scans – two at baseline and another at the end of treatment.

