**Outcome Measures**

The primary outcome measure will be continuous abstinence from smoking during weeks 9 – 12 as reported at clinic visits during those 4 weeks and confirmed using expired CO. Subjects will be classified as treatment responders if they respond “no” to the question: Have you smoked any cigarettes (even a puff) in the last seven days?

The key secondary outcome measures are:

1. Self-reported 7 day point prevalence abstinence throughout weeks 2 to 12 confirmed by expired CO at each clinic visit. To calculate survival curves we will also collect self-reported continuous abstinence weeks 9 through 26. For weeks 13 to 25, this will be collected via email or text message. For week 26, subjects will attend a brief clinic visit so abstinence can be confirmed with expired CO and urinary cotinine using a semi-quantitative dipstick. We hypothesize that the active tDCS group will have higher rates of abstinence (less relapse) than the sham tDCS group.

2. fMRI: change in Blood Oxygen Level Dependent (BOLD) activation in brain regions known to be associated with drug craving and emotion processing/regulation. MRS: GSH levels measured in a single voxel placed over prefrontal cortex. Fractional anisotropy (FA) values will be extracted from DTI analysis from regions of interest (ROIs) or to form probabilistic tractography for the whole brain. Network maps will be extracted and analyzed from the resting state functional connectivity measure.

3. Eye Tracking tests: changes in attentional bias to smoking-related cues and negative emotional cues. Attentional bias to high-arousal/high-risk cues.

*Self-Report Measures*

Participants will complete the 10-item Questionnaire of Smoking Urges-Brief (QSU-10; Tiffany and Drobes, 1991) and the Minnesota Nicotine Withdrawal Scale (MNSW; Toll et al, 2007) at each treatment session upon arrival and immediately after tDCS. They will complete a Side Effects Checklist ([name] et al., 1995) at the end of each treatment session.

Trait scales to be completed at baseline will include the FTND (Heatherton et al 1991) and Alcohol Use Disorders Identification Test (Saunders et al., 1993), 90-day Alcohol Timeline Followback (TLFB; Sobell and Sobell, 1992); 30-day Tobacco Timeline Followback (adapted from alcohol TLFB); Sensation Seeking Scale (Zuckerman et al., 1978).

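### The imaging comparison of active with sham tDCS names no baseline adjustment, so it is valid but less efficient than the two pre-treatment scans would allow

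*Protocol*

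**What the plan says.** Under Design, the protocol states: "Participants will undergo two scans at baseline on different days within the same week: one in a satiated state and one in a non-satiated state". Eligibility criteria repeat the count: "Willing to undergo three fMRI scans – two at baseline and another at the end of treatment". Both baseline scans precede any treatment: "Following the baseline fMRI scans and eye-tracking tests, subjects will start taking the varenicline simultaneous with starting the tDCS regimen".

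The imaging hypothesis has a within-subject part and a between-arm part: "Active tDCS will reduce fMRI BOLD response to smoking cues compared to baseline within-subjects and compared to sham tDCS between subjects". The Outcome Measures section defines the endpoint as a change: "fMRI: change in Blood Oxygen Level Dependent (BOLD) activation in brain regions known to be associated with drug craving".

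For analysis, the Data Analysis section says that "brain imaging measures will be compared between groups and across time points, using analysis of variance". Earlier in that section it adds: "Planned comparisons will be performed for the critical experimental conditions (active tDCS) vs. sham". It does not give the levels of the time factor for imaging, the term or contrast that tests active against sham, or any baseline covariate. Later in the section the expected advantage of active tDCS is placed at the second MRI scan, although three scans are planned and the end-of-treatment scan is the third.

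**The concern.** Treatment begins only after both baseline scans. In a randomised comparison, any arm difference between the abstinent and the satiated baseline scan is therefore chance. A group-by-time test with three levels of time has two interaction degrees of freedom, and one of them is that pre-treatment difference. It carries no treatment signal but still raises the critical value.

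A change score avoids this but fixes the baseline coefficient at 1, where ANCOVA estimates it. When scans correlate only moderately, a coefficient of 1 over-corrects and adds noise.

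With at most 25 per arm, the imaging comparison has little precision to spare. The Sample Size section calls 15 to 25 per group more than sufficient for between-group differences, but shows no calculation for imaging. At stake is a higher chance of a null between-arm imaging result than the planned scans require.

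**Working it through.** **The protocol's own power figure.** The only one concerns abstinence: 40% against 80%, 25 per arm, 80% power. The normal approximation gives n = [1.96·√(2·0.6·0.4) + 0.8416·√(0.4·0.6 + 0.8·0.2)]² / 0.4² = (1.358 + 0.532)² / 0.16 = 22.3, so 23 per arm. Exact Fisher power at 25 per arm is 78.8%. The stated figure is reproduced, but it says nothing about imaging.

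**Inputs for imaging.** From the protocol: three scans, two of them before treatment; 25 per arm; two-sided 0.05 (stated in Data Analysis for estimating a later sample size). Assumed, because the protocol gives neither: a true arm difference d at the third scan only, in SD units, and a correlation r between scans. Variance is set to 1, r is first taken as equal for all pairs of scans, and no scan is missing.

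**Formulas (n per arm).**
- 2-df group-by-time test: noncentral F(2, 96) with λ = n·d² / [3(1−r)].
- The other three: noncentral t with noncentrality d·√(n/(2v)), where v is the per-person variance.
- Change from one baseline: v = 2(1−r), 48 df.
- Change from the mean of both baselines: v = 1.5(1−r), 48 df.
- ANCOVA on both baselines: v = 1 − 2r²/(1+r), 46 df.

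**Worked case, d = 0.5, r = 0.5.**
- 2-df test: λ = 25·0.25/1.5 = 4.17, power 41.9%.
- Change from one baseline: v = 1.00, noncentrality 0.5·√12.5 = 1.77, power 41.0%.
- Change from the mean: v = 0.75, noncentrality 2.04, power 51.6%.
- ANCOVA: v = 1 − 0.5/1.5 = 0.667, noncentrality 2.17, power 56.3%.

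**Power (%) over the range.**

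| d | r | 2-df test | Change, one baseline | Change, mean of both | ANCOVA, both | Gain over 2-df | Gain over mean change |
|---|---|---|---|---|---|---|---|
| 0.5 | 0.3 | 31.0 | 31.0 | 39.4 | 46.2 | 15 | 7 |
| 0.5 | 0.5 | 41.9 | 41.0 | 51.6 | 56.3 | 14 | 5 |
| 0.5 | 0.7 | 63.7 | 60.9 | 73.3 | 75.8 | 12 | 2.5 |
| 0.8 | 0.3 | 68.0 | 64.9 | 77.2 | 84.7 | 17 | 7.5 |
| 0.8 | 0.5 | 82.9 | 79.1 | 89.3 | 92.4 | 9.5 | 3 |
| 0.8 | 0.7 | 96.9 | 94.7 | 98.5 | 98.9 | 2 | 0.4 |

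Over the same r, the ANCOVA variance is 6% to 18% below that of change from the mean, and 29% to 38% below that of change from one baseline.

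**Outside the table.**
- d = 0.6, r = 0.3: the gain over the 2-df test is 18 points, and over change from the mean 8.
- d = 1.0, r from 0.3 to 0.7: the gain over the 2-df test falls from 9 points to 0.2.
- 15 per arm, d = 0.5, r = 0.5: 26% for the 2-df test against 37% for ANCOVA.

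**Unequal correlations.** One baseline scan follows abstinence and the other is satiated, so equal r is doubtful. Simulation used 20,000 runs per case, 25 per arm, and ANCOVA on the mean of the two baselines:
- Baselines correlate 0.7 with each other and 0.5 with the third scan: gain over the 2-df test 7.1, 8.8 and 6.2 points for d = 0.5, 0.6 and 0.8.
- Baselines correlate 0.4 with each other and 0.6 with the third scan: gain 23.2, 20.3 and 7.5 points. Here ANCOVA and change from the mean are practically equal (0.6, 0.2 and 0.0 points apart).

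The F test in these runs was not corrected for non-sphericity, so these unequal-correlation figures are approximate.

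**The case against.** The strongest reply is that the three-level model is inferred. The protocol names no two-by-three layout and no 2-df interaction as the test. Its Background speaks of comparing pre- and post-treatment scans, its outcome is a change, and it foresees planned active-versus-sham comparisons. A single contrast of the final scan with the mean of both baselines would leave ANCOVA an advantage of at most about 8 points. The exact model may also sit in an analysis plan that is not shown. This stands as far as it goes: no single power loss can be charged to the protocol. It does not remove the point. The one group-level method that the protocol states for the arm comparison is an unadjusted ANOVA, and averaging the baselines is stated nowhere. A change from one baseline would leave ANCOVA about 15 points ahead at 0.5 SD.

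A reader might infer that the plan does nothing with the baseline scans to remove between-person variance. That is not so. A repeated-measures or change analysis removes some of it, which is why the power of the 2-df test rises from 31% to 64% as r goes from 0.3 to 0.7 at 0.5 SD. ANCOVA simply removes more.

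Two further objections stand. Power for one scalar measure does not carry over to a whole-brain voxelwise analysis. And ANCOVA at the final scan cannot answer the within-subject questions: change from baseline in Hypothesis 2, and the effect of varenicline within the sham arm described in the Background. The time comparison must therefore stay as an analysis in its own right.

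**Conclusion.** The point holds as one of efficiency. The stated ANOVA is valid, and randomisation protects it from bias. It names no baseline adjustment for active versus sham, although two pre-treatment scans per person are available to supply one. Under equal correlation, ANCOVA on both baselines had the highest power in every case calculated. In the unequal-correlation cases it always beat the 2-df test and at worst roughly matched change from the mean.

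A reader might carry away a flat loss of 12 to 17 power points. The documents do not support that figure as a property of this plan. It needs an effect near 0.5 to 0.6 SD, moderate equal correlations, 25 complete participants per arm and the 2-df test, and the protocol fixes neither the effect, the correlations nor the test. Across all cases examined, the gain over the 2-df test runs from about 0 (1.0 SD, r = 0.7) to about 23 points (0.5 SD, unequal correlations). Over a change from the baseline mean it runs from about 0 to 8.

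Imaging is a secondary objective in a 50-person pilot, so the change is worth making but does not correct an error.

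**What to change.** In the MRI part of Data Analysis, name the active-versus-sham imaging estimate: the end-of-treatment value of each measure, compared between arms by ANCOVA, with that measure's abstinent and satiated baseline values as two covariates. Apply it to region-of-interest measures, and voxelwise where feasible. Entering both values also avoids having to choose which baseline state the final scan should be set against.

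Keep the within-subject comparison over time for the hypotheses that need it, and say which scans enter it. Replace the reference to the second MRI scan with the end-of-treatment (third) scan.

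The cost is two residual degrees of freedom (48 to 46 with complete data) and some extra modelling for voxelwise analyses, where the covariates differ at each voxel. No further scans or participants are needed.
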